#### Phase II - statistical analysis of the secondary endpoints

Toxicity analyses will be performed. As for acute toxicity, late AE and grading will be reported at each follow up visit. Median survival time and its 95% bilateral confidence intervals (PFS, clinical PFS, local PFS, OS, and PCSS) will be determined using the *Kaplan Meier* method. The rate of survival will be given at 1, 2, 3, and 5 years. Univariate and multivariate *Cox* regression models will be fit to assess the effect of relevant baseline clinical and pathologic features on bRFS, PFS, and OS. Hazard ratio (HR) will be given with their 95% confidence intervals. Median follow-up will be estimated using the reverse *Kaplan Meier* method. QoL scores (EPIC, IPSS, IIEF-5) will be described at each clinical surveillance follow-up time by the mean, standard deviation, median, and range. Domain scores will be calculated only if sufficient items are completed in accordance with the relevant scoring manual. Mixt models will be used to characterize changes in QoL across time taken into account for confounding clinical and pathologic factors. All statistical analysis will be performed with SAS 9.4. *p*-values less than 5% will be considered as significant.

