Indeed, preliminary results on extreme hypofractionation with SBRT have been reported during the last few years mainly for low-risk patients in single-institution [6–8] or multi-institutional [9] series. Most frequently, 5 fractions of 7.25 Gy have been delivered for a total equivalent dose to the tumor of 90 Gy in 2 Gy/fraction (LQ model) and a success rate of > 90%, 5-year biochemical relapse-free (bRFS) survival rates [10]. Data published so far for prostate SBRT have shown, although with a limited follow-up, late grade 3 toxicity rates for rectal and genitourinary (GU) toxicity lying within a ≤ 3% range [8, 11, 12]. Although, caution is recommended to avoid passing a too optimistic message regarding the potential biological benefits of extreme hypofractionation for prostate cancer (i.e., more cure with less side effects), financial and logistical advantages can undoubtedly be foreseen. In fact, a drop from 40 or more treatments to 5 or less sessions may reduce the cost of external beam RT, will increase the availability of treatment slots in otherwise busy departments (important issue in countries with limited resources), and significantly improve patient’s convenience.

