The question of how far can the number of fractions with SBRT be reduced is an exciting research matter with an undoubtful goal, face the challenge of assessing the potential for cure of prostate cancer patients with a single and unique fraction of high dose irradiation similar to what is already undertaken with radiosurgery against brain, lung, and liver targets. Such type of effort has already been attempted with HDR-BT. Recently, Prada et al. [13] reported a relatively disappointing 66% 6-year bRFS survival though a very good tolerance after a single interstitial application of 19 Gy to the prostate. Reasons for this suboptimal result may be related, for instance, to a suboptimal dose-distribution with HDR-BT compared to SBRT. Hoskin et al. have recently published the results on 49 patients treated with a single fraction of HDR-BT to 19/20 Gy [14]. With 49 months median follow-up, the 4-year estimates of grade-3 GU and gastrointestinal (GI) toxicity was 2% and 0%, respectively, with no grade 4 events, while the 4-year bRFS was 94%. Similarly, Morton et al. confirmed with a median follow-up time of 20 months the good tolerance of a single 19 Gy single HDR-BT fraction in terms of toxicity and impact on quality of life (QoL) [15] and Krauss et al. reported a 3-year bRFS rate of 93% [16], similar to results observed by Hoskin et al. In conclusion, for the authors one single fraction HDR-BT is feasible, weakly toxic, and with promising preliminary results.

Although, the effects are mostly encouraging, only controlled studies are able to properly address the impact of single fraction SBRT in prostate cancer outcomes. Therefore, a phase I/II approach will be a properly controlled study to demonstrate early evidence of safety and efficacy of the intervention and substantiate further the role of a single-fraction SBRT approach. If positive, the results of ONE SHOT will help determine the design of subsequent phase III trials in the exclusive RT setting for the treatment of localized disease.

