#### Follow-up

Patients are seen at day-5 after SBRT, at weeks 6 and 12, every 6 months for 2 years post treatment, and yearly up to 5 years of follow-up. A clinical update and a physical exam are conducted by recording any acute and/or late AE and the sequential PSA measurements. IPSS, IIEF-5, and QoL (EPIC-26 questionnaire) assessments are also performed. Radiological investigations including mpMRI, bone scan, choline-PET, and/or PSMA-PET will be repeated in case of progression, either biochemical or clinical.

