#### Phase I

Safety analyses shall be performed on the safety-evaluable population, defined as all subjects treated with the single shot SBRT. Toxicity and grade will be described at each follow-up visit according to the specificity of every assessed endpoint, including the number and fraction of patients with at least one AE.

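### Late toxicity is specified visit by visit, with no cumulative estimate or confidence interval, so resolving late events would not be reported like for like with the 4-year grade 3 figures cited in the Background

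*Protocol article*

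**What the plan says.** Late AEs, meaning those after 3 months graded by CTCAE v4.03, are a phase II secondary endpoint (Secondary endpoints of the phase II trial). Their analysis is one sentence in the section on statistical analysis of the secondary endpoints. It opens by referring back to acute toxicity and continues: "late AE and grading will be reported at each follow up visit".

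The back-reference appears to point to Data analysis, Phase I. There, toxicity and grade are described at each visit in all treated patients, "including the number and fraction of patients with at least one AE". That sentence does not say whether the fraction is taken per visit or over all follow-up.

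In the secondary-endpoint section, Kaplan-Meier is assigned to PFS, clinical PFS, local PFS, OS and PCSS, with rates at 1, 2, 3 and 5 years. Late toxicity is not in that list.

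Follow-up sets visits at day 5 and weeks 6 and 12, then "every 6 months for 2 years post treatment, and yearly up to 5 years of follow-up", each "recording any acute and/or late AE and the sequential PSA measurements".

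The Background cites two toxicity results. For single-fraction HDR brachytherapy, "the 4-year estimates of grade-3 GU and gastrointestinal (GI) toxicity was 2% and 0%, respectively". For prostate SBRT, "late grade 3 toxicity rates for rectal and genitourinary (GU) toxicity lying within a ≤ 3% range".

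**The concern.** Safety is half of the trial's stated aim, and the phase I rule covers only acute events in the first 3 months. Any message about later harm rests on this secondary endpoint.

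A percentage at a visit and a cumulative incidence answer different questions. The first says how many patients have the problem then (or since the last visit); the second says how many have had it by a given time. For problems that come and go, a run of low visit percentages can accompany a much higher proportion of patients ever affected. Readers will naturally set the late results beside the cited 4-year figures, which are time-based estimates, and the quantity the plan describes is not the same one. If the choice of summary is left open until results are known, the more favourable one may also be picked.

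**Working it through.** The plan states no rate, precision or sample size for late toxicity, so there is no figure of its own to reproduce. The question is how far visit percentages can sit below cumulative incidence on the plan's own schedule.

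**Inputs from the document.** Late visits at months 6, 12, 18, 24, 36, 48 and 60 (seven visits, Follow-up); late period from month 3, so 57 months to month 60; 45 patients and 10% dropout (Sample size, phase II).

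**Assumptions not in the document.** Constant hazard of a first late event from month 3 to 60; one episode per patient with exponentially distributed duration.

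**1. Prevalence at a visit.** Let F be the 5-year cumulative incidence, λ = −ln(1−F)/57, d the mean duration in months, μ = 1/d, and s the months since month 3. The proportion with the event present is

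P(s) = λ/(μ−λ) × (e^(−λs) − e^(−μs)).

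For F = 10%, λ = 0.10536/57 = 0.001848 per month. With d = 24, at month 60 (s = 57): 0.001848/(0.041667 − 0.001848) × (0.900 − 0.093) = 0.0464 × 0.807 = 3.7%. The highest value over the seven visits is:

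| Mean duration | F = 10% | F = 20% |
|---|---|---|
| 3 months | 0.5% | 1.1% |
| 6 months | 1.0% | 2.1% |
| 12 months | 2.0% | 4.0% |
| 24 months | 3.7% | 7.3% |
| Permanent | 10% | 20% |

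**2. If each visit records new events since the last one.** The largest row is the 24-to-36-month interval: e^(−21λ) − e^(−33λ) = 0.962 − 0.941 = 2.1% for F = 10%, and 4.2% for F = 20%. No single row shows the total, but the rows add up to F in the absence of dropout.

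**3. Limiting case.** Suppose a fraction p of patients has an event in each of the seven intervals, independently of earlier events, and it shows at one visit only. Every row then shows p, while the proportion ever affected is 1 − (1−p)^7: for p = 4%, 1 − 0.96^7 = 24.9%; for p = 2%, 1 − 0.98^7 = 13.2%. This is the extreme end, because everything must resolve before the next visit, across gaps of up to 12 months.

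**4. If the fraction with at least one AE covers all late follow-up.** With 10% lost between months 3 and 60 at constant hazard c, the crude fraction is λ/(λ+c) × (1 − e^(−57(λ+c))). For F = 10%, c = λ, giving 0.5 × (1 − 0.81) = 9.5%. For F = 20%, 0.003915/(0.003915 + 0.001848) × (1 − 0.72) = 19.0%. The shortfall is 0.5 to 1 percentage point, or at most 0.45 of a patient in 45.

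**5. Precision.** With 0 events in 45, the exact upper limit is 1 − 0.025^(1/45) = 7.9%. With 1 in 45 (2.2%), the exact 95% interval is 0.1% to 11.8%. These widths come from the sample size and hold for any summary, but the plan gives no interval that would show them.

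**The case against.** The strongest reply is that this is an omission from a condensed article. The analysis plan is not shown, a visit table is legitimate in itself, and cumulative summaries of a secondary safety endpoint are often left to the analysis plan. That limits the severity but does not remove the point: the article does state a method for late toxicity, and in the same paragraph specifies time-to-event methods for other secondary endpoints.

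Several stronger readings are tempting, and the document does not support them.

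- *Late toxicity is only tabulated by visit.* The sentence refers back to acute toxicity, whose description includes a fraction with at least one AE. If that fraction covers the whole late period, little is lost (step 4). Against this, it sits in a sentence about each follow-up visit under the phase I heading, so the text is ambiguous rather than restrictive.
- *Late harm will be understated.* That depends on event duration and on whether visits record current or interval events. Permanent events leave no gap at the last visit.
- *The results cannot be compared with the literature.* AEs are recorded at visits to 5 years, so a cumulative estimate can be derived from the planned data.
- *The cited benchmarks are cumulative.* Only the HDR brachytherapy figures are given as 4-year estimates. The SBRT range of 3% or less is not labelled crude, prevalent or cumulative. No formal comparison with either is planned.

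It is also fair that grade 3 rates of 0 to 3% mean about one event in 45 patients (0.03 × 45 = 1.35), and a single patient is easy to identify in a visit table. The gap matters more for grade 2 events, which can be expected to be more frequent.

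**Conclusion.** The point holds in a limited form and is minor. As written, late toxicity is described by visit, without a cumulative estimate or interval, and the reach of the fraction with at least one AE is unclear. For events that resolve, visit percentages can be several times lower than the cumulative rate: 0.5% to 3.7% against 10%, or 1.1% to 7.3% against 20%, for mean durations of 3 to 24 months. These figures rest on an assumed constant hazard and assumed durations. The gap closes at the last visit for permanent events and nearly closes if a per-patient fraction over all late follow-up is reported. What follows is that the stated summary is not like for like with the 4-year grade 3 estimates in the Background. It does not follow that late toxicity will be understated or that comparison is impossible. The primary endpoints, sample size and data collection are unaffected.

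**What to change.** Keep the visit table and add to the section on secondary endpoints:

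- cumulative incidence of the first late grade 2 or higher AE and the first late grade 3 or higher AE, for GU and GI separately, counted from 3 months after SBRT, with death as a competing event and censoring at loss to follow-up, reported at 1, 2, 3 and 5 years with 95% confidence intervals (a 4-year value can be read from the same curve for the cited series);
- worst late grade per patient;
- a statement of whether the fraction with at least one AE is per visit or over the whole late period, and whether visits record current events or events since the last visit.

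If the analysis plan already contains this, a cross-reference is enough. The cost is a few sentences and a few more tables from data already collected. The small downside is that the cumulative figures will look less favourable than the visit figures.

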##### Primary endpoint of the phase II trial

bRFS, from time of inclusion until biochemical progression (according to recommendations of the Radiation Therapy Oncology Group - American Society for Radiation Oncology (RTOG-ASTRO), the Phoenix Consensus Conference recommendations) [17]:A rise by 2 ng/ml or more above the nadir prostate specific antigen (PSA) confirmed by a second observation taken 3–4 weeks later, where the nadir PSA is defined as the lowest PSA value observed on study.

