### Phase II, efficacy evaluation

Based on published SBRT results on 5 fraction-trials and on one series of HDR-BT with 19 Gy single shot, a 3-yearsbRFS of 96% may be expected. Assuming this hypothesis and an expected dropout rate of 10%, 45 patients (including the 6 included in the phase I study) will allow evaluating 3-year bRFS with a 97.5% lower one-sided confidence interval and a width of the interval of 0.06 (upper bound = 90%).

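### A multivariable Cox model is planned for bRFS, but the trial's own 96% assumption implies about two events at 3 years, so adjusted hazard ratios could not be estimated reliably

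*Protocol article*

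**What the plan says.** Under *Phase II - statistical analysis of the secondary endpoints*, the article says of univariate and multivariate Cox that "regression models will be fit to assess the effect of relevant baseline clinical and pathologic features on bRFS, PFS, and OS". Hazard ratios are to be given with 95% confidence intervals. The same section closes with a general rule for p-values: "values less than 5% will be considered as significant". The models are stated as firm analyses and are not called exploratory.

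Under *Phase II, efficacy evaluation* (sample size), the planning assumption is that "a 3-yearsbRFS of 96% may be expected". The trial takes 45 patients, 6 of them from phase I, and allows for 10% dropout.

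Two further statements fix how many events there can be. The primary endpoint is defined as "bRFS, from time of inclusion until biochemical progression", so death is not named as a bRFS event. Under *Follow-up*, visits run "every 6 months for 2 years post treatment, and yearly up to 5 years of follow-up".

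**The concern.** The precision of a Cox model depends on the number of events, not the number of patients. The sample size section plans for a treatment that almost never fails biochemically within 3 years. The secondary analysis section then plans to explain those failures by several baseline features at once. If the first holds, the second has almost no data to work on.

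Followed as written, the analysis would produce hazard ratios that are either infinite or so imprecise that they carry no information, and would then judge them at 5%. The article says the results may help design phase III trials, so a table of adjusted hazard ratios from two or three events could be given more weight than it deserves.

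**Working it through.** **Inputs from the article.** N = 45; 3-year bRFS 96%; 10% dropout; 97.5% one-sided limit at 90%, i.e. 0.06 below the estimate; follow-up to 5 years; the cited 6-year bRFS of 66% after single-fraction brachytherapy (*Background*). **Assumptions of this review.** Constant hazard beyond 3 years; balanced, independent, non-prognostic binary covariates. The article names no covariates, so the latter are illustrative.

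**1. The plan's own figure.** n = 1.96² × 0.96 × 0.04 / 0.06² = 40.98, so 41 evaluable patients. Allowing for dropout, 41 / 0.9 = 45.6 or 40.98 × 1.1 = 45.1. The stated 45 is reproduced to within one patient, so the 96% is the assumption that sized the trial.

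**2. Expected bRFS events.**
- By 3 years: 45 × (1 − 0.96) = 1.8; with 41 evaluable, 1.6.
- By 5 years, constant hazard: S(5) = 0.96^(5/3) = 0.934, so 45 × 0.066 = 2.96; with 41 evaluable, 2.7.
- If the hazard doubled after year 3: about 4 by 5 years.
- Binomial, N = 45: the chance of at most one event is 46% by 3 years and 20% by 5 years. The chance of 10 or more by 5 years is below 0.1%.

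**3. Precision with one balanced binary covariate.** SE(log HR) = √(4/d), where d is the number of events; the 95% interval is the estimate multiplied and divided by exp(1.96 × SE).
- d = 2: SE = 1.41, factor 16.
- d = 3: SE = 1.15, factor 9.6. Power to detect a hazard ratio of 3 is 16%.
- By Schoenfeld's formula, 80% power needs 27 events for a hazard ratio of 3 and 66 for a hazard ratio of 2.

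**4. Infinite estimates.** If all d events fall in one category of a binary covariate, its hazard ratio is zero or infinite. For a balanced covariate the chance is 2 × 0.5^d.
- One covariate: 50% with 2 events, 25% with 3.
- Three covariates, at least one infinite: 1 − 0.5³ = 87.5% with 2 events; 1 − 0.75³ = 58% with 3.
- Averaged over the binomial event count, with fewer than two events counted as failure, all three estimates are finite in 18% of data sets at 3 years and 39% at 5 years.

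**5. If the treatment does worse than planned** (constant hazard, events by 5 years, N = 45).
- 3-year bRFS 90%: 45 × (1 − 0.90^(5/3)) = 7.2.
- 3-year bRFS 85%: 45 × (1 − 0.85^(5/3)) = 10.7.
- The cited 66% at 6 years: 45 × (1 − 0.66^(5/6)) = 13.2. With 13 events the interval factor for one balanced covariate is still about 3.

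**6. OS and PFS.** The article gives no rate for either. If 5-year OS lay between 85% and 98% (assumed), deaths would number 45 × 0.15 = 6.8 down to 45 × 0.02 = 0.9. PFS adds deaths, clinical progression and new systemic therapy to biochemical progression, so it cannot have fewer events than bRFS.

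**The case against.** The strongest reply is that this is a journal article. The choice of covariates, a minimum event count and a penalised method are normal content for an analysis plan that is not shown. That stands as far as it goes: their absence is not the fault. The fault is in what the article does state, namely multivariable models for bRFS with intervals and a significance rule, beside a planning rate that leaves almost no events.

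A reader might infer that the hazard ratios cannot be estimated at all. The documents do not support that. A balanced binary covariate gives a finite estimate half the time with 2 events and three-quarters of the time with 3. Continuous covariates such as PSA or age rarely give an infinite one: in simulated sets of 45 patients with three such covariates, about 5% or less. There the trouble is imprecision. Nor can the model be called saturated, since the number of covariates is not stated.

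A reader might also infer that the planning assumption rules out the OS model. It does not: the 96% concerns bRFS, which does not count death, and men up to 85 years are eligible. Likewise, the count of 3 at 5 years is not the trial's own figure, since the article assumes only a 3-year rate.

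Two further points stand in part. When an estimate is infinite, its Wald p-value drifts towards 1, so uninterpretable output is a likelier result than a false prognostic factor, and the planned intervals would show the imprecision. And if results are poor, about 11 to 13 events could accrue by 5 years. That could support a cautious look at one covariate, but is still thin for a multivariable model.

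**Conclusion.** The concern holds for the multivariable bRFS model. On the trial's own 3-year rate about 1.8 events are expected, and that alone is enough for the conclusion. The figure of about 3 by 5 years adds a constant hazard, and doubling the later hazard changes it only to about 4. Adjusted hazard ratios from such data cannot be estimated reliably. The 58% to 87.5% chance of at least one infinite hazard ratio rests on three balanced, independent binary covariates and would differ with others.

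For OS and PFS no conclusion can be drawn in advance, and the observed counts must decide. These are secondary analyses: the primary Kaplan-Meier estimate, the sample size and the safety rules are not affected. This is a cheap improvement, not a threat to the trial's main result.

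**What to change.** Replace the multivariable Cox model for bRFS with a table of biochemical failures by baseline factor. If the observed events allow, fit one prespecified covariate at a time by Firth-penalised Cox with profile-likelihood intervals. Label these results exploratory and exempt them from the 5% significance rule. State that the observed number of events decides whether the same limit applies to PFS and OS.

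The cost is a change of wording and somewhat less analysis. No adjusted hazard ratios for bRFS would be reported, but at the expected event counts they would be uninformative. Data collection, sample size and the primary analysis stay as they are.

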## Discussion

Optimal management of localized low- or intermediate risk prostate cancer remains a challenging situation, with different treatment options available ranging from active surveillance to radical treatment [25]. Considering that patients under active surveillance have a greater risk of disease progression and metastases compared to definitive treatments [26], the choice of the more appropriate curative option is a crucial issue for clinicians.

SBRT represents a valid treatment option for these patients, combing a good toxicity profile, promising disease control rates, and limited impact on QoL. Recently reported, preliminary results of the Scandinavian phase III HYPO-RT-PC trial found in 1200 intermediate-risk prostate cancer patients similar biochemical control rates and toxicities results with extreme hypofractionation (42.7 Gy in seven fractions of 6.1 Gy over two and a half weeks) compared to standard fractionation 78 Gy [27]. However, the optimal SBRT fractionation schedule for curative treatment of patients with localized prostate cancer is, so far, unknown. Based on the promising results of HDR-BT monotherapy treatments [15, 28, 29], single-shot SBRT may represent an appealing treatment modality for prostate cancer patients.

To our knowledge, ONE SHOT is the first phase I/II trial assessing the efficacy and safety of a single-dose SBRT treatment for patients with localized prostate cancer in a multicenter setting. ONE SHOT proposes the same treatment technique under a strict RTQA protocol for all patients. By reducing significantly the beam-on time [30], our single shot linac-based FFF VMAT technique with intra-fractional control motion is expected to guarantee not only treatment reproducibility [31] but also minimize intra-fraction dose uncertainties [32]. Moreover, the implementation of patient-reported outcome using validated questionnaires will provide a reliable evaluation of the clinical impact of a single-dose SBRT by reporting a longitudinal follow-up on the long-term of radiation-induced side effects compared to physician-reported data.

While waiting for results of presently ongoing randomized phase III trials comparing SBRT with other fractionation or treatment, results of the ONE SHOT trial, if positive, may help to design subsequent studies exploring the role of SBRT monotherapy in the exclusive RT treatment of localized disease.

